**Table 2. Guidance for Safety and Adverse Event Reporting and Serious Breaches of Protocol**

| Type of Event | Example | How | When |
| --- | --- | --- | --- |
| Adverse Event | Complaints from the participants that indicate the negative impact of app usage on mental health | Email to the DSMB and the UNSW Human Research Ethics Committee | Within 24 business hours of becoming aware of the event |
| Investigator’s Brochure Updates/Addenda | - | Email to the UNSW Human Research Ethics Committee | Annually with the annual safety report, or as required. |
| Annual safety report | - | Annual Progress Report | Annual as required by the HREC |
| Serious Breach of Protocol | - | Email to the DSMB and the UNSW Human Research Ethics Committee | Within 24 business hours of becoming aware of the event |

# Risk management

## 12.1. Risk mitigation strategies

To minimise known harms, risks, and discomfort to participants, the below procedures will be implemented in the study. In both the control and intervention apps there is a help button that contains a directory of key sources of help such as phone numbers for Kids Helpline and LifeLine to ensure that participants have access to support 24/7. Participants are also reminded of contacting their GPs when feel distressed and maintaining their regular medicine during the trial.

In addition, there is a “get help now [panic button]” under this “help button”. When young people click the “get help now button”, a screen will pop up in the app to seek confirmation that they want to be contacted by a clinical psychologist during business hours. Once confirmed, a text message containing young people’s contact number will be sent to the clinical psychologist. They will be contacted by the clinical psychologist within the next 24 business hours.

In the middle of the trial (3-weeks after baseline assessment), young people will be asked to complete a safety check (approximately 1 minute) to assess their suicidal thoughts (using the SIDAS screener). If they report a SIDAS score above 20 they will be contacted by a clinical psychologist to refer them to appropriate psychological support, if they consent.

In addition, an independent Data Safety and Monitoring Board (DSMB) will be established to monitor the safety of research participants. DSMB membership will consist of 3 external members who are experts in clinical trial conduct, statistics, and youth mental health. The research team will record the number of notifications and notify the DSMB when each assessment period is complete. The DSMB will provide recommendations to the research team to continue, temporarily pause conduct of the trial, or discontinue, pending risk issues or adverse events. The research team will record all risk alerts in a case report which will be securely stored on the Black Dog Institute’s UNSW server.

The DSMB Charter is attached as Appendix E.

## 12.2. Privacy, confidentiality, and data management

The sensitive data collected by this study includes participants' responses to the personal detail questionnaire, their responses to the surveys, and the audio records of the interviews. This data is collected by the Black Dog Institute e-health platform. It is stored on UNSW servers (MED/BDI) and protected by encryption.

Each participant will be assigned a unique identification code automatically at the time of registration on the Black Dog Institute research platform. When online survey data is exported for analysis, the chief investigator will remove the identifiable information from this initial data set (I.e. remove first name, mobile phone number, and email address).

A de-identified copy of the data will be downloaded for analysis on the UNSW OneDrive, which is password protected and approved by the University for storing highly sensitive data. The file used for analysis will only include the unique ID code and raw research data. Only named study personnel will have access to any identifiable information. For participant withdrawal, only named study personnel will access the register to identify the personal details of participant using their ID code.

The transcription of the interviews will be undertaken by a professional transcription service, and only deidentified audio will be provided to the agency. The agency will be asked to sign a confidentiality agreement before being provided with the recordings. Participants will be informed that deidentified audio will be provided to an agency for transcription service only. Upon completion of this project, all information will be stored in an archive on the server hard drive for a period of a minimum of 7 years, in accordance with UNSW and the Australian Code for the Responsible Conduct of Research.

# Appendix A: Recruitment materials

**The LifeBuoy App: A randomised controlled trial of a mHealth intervention to help young people manage suicidal thoughts**

We are looking for young people who have experienced suicidal thoughts to participate in a study evaluating the effectiveness of a smartphone app “LifeBuoy” that is designed to reduce suicidal thoughts.

We need young people who:

- Are 16-25 years old;
- Are living in Australia;
- Are fluent in English;
- Own and have access to a smartphone;
- Have experienced suicidal thoughts in the past year;
- Have not been diagnosed with psychosis or a bipolar disorder;
- Have no suicidal attempt or plan in the past month.

Eligible participants will:

1. Be assigned to one of two groups: an intervention group (who receives the therapeutic app) or a control group (who receives a non-therapeutic app). All participants will then follow the same process;
2. Complete 7 modules in the app over 6 weeks (total 1 hour);
3. Complete an online survey on 3 occasions: before (35 minutes) and after completing all modules (25 minutes), and then 3 months after the completion of all modules (25 minutes). The survey will include questions about your demographics, suicidal thoughts and suicide attempts, negative life events, how you have been feeling lately, sleep, help-seeking intentions and experience, perseverance, and expectations of and satisfaction with the app;
4. Download an app called ‘Lifebuoy’ after completing the first survey, (you will not know whether you are receiving the intervention or control version of this app). Both apps will be available for 6 weeks for use on your personal smartphone. If you receive the control app, you will be informed after the final survey to let you know that you were in the control condition, and what that means.
5. Receive a $20 gift card in acknowledgement of your time and internet expenses related to participation in each follow-up survey (total $40 gift card if you complete both follow-up surveys).

Please note: suicide related questions will be asked in the online survey. Participants are free to withdraw at any time. The identified information obtained in this study will remain confidential and be stored in an archive on the UNSW server hard drive for a period of 7 years.

If you are interested in participating this study, please click here <Insert link: XXX>.

This study has been approved by Human Review Ethics Committee at the University of New South Wales [HC190764]

**Advertisement for social media channels**

The Black Dog Institute is inviting young people aged 18-25 who have experienced suicidal thoughts to participate in a study evaluating the effectiveness of a smartphone app designed to reduce suicidal thoughts. You will receive $40 in appreciation for your time in participating. This study involves the completion of 7 app modules over 6 weeks (1 hour total), and one online survey before starting the app (35 minutes) and two surveys after (immediately and 3-months later; 25 minutes each).

Click here <Insert the link to the recruitment page> to get more information. Lifeline: [name].

**Short version of the advertisement**

The Black Dog Institute is inviting young people aged between 16-25 who have experienced suicidal thoughts to evaluate the effectiveness of a smartphone app designed to reduce suicidal thoughts. You will receive $40 in giftcards for participating.

Click here<Insert the link to the recruitment page> to know more. Lifeline: 13 11

# Appendix B: Screening and Eligibility

**Screening questions**

| **What the participant will see** | | **Drop down response options available** |
| --- | --- | --- |
| Are you aged between 16 and 25? | --- select --- | Yes, I’m between 16 and 20 years old  Yes, I’m between 21 and 25 years old  No |
| Are you living in Australia currently? | --- select --- | Yes  No |
| Are you fluent in English? | --- select --- | Yes  No |
| Do you own, or have access to, a smartphone (iOS or Android)? | -- select --- | Yes  No |
| Have you experienced suicidal thoughts in the past 12 months? | -- select --- | Yes  No |
| Have you attempted suicide in the past month? | -- select --- | Yes  No |
| Have you ever been diagnosed with psychosis or bipolar disorder? | -- select --- | Yes  No |
| Gender assigned at birth | -- select --- | Male  Female |

**Wording following screening outcomes**

**(If eligible)**

Ok great, thank you so much for taking the time to do that.

Based on your responses, it looks like you are:

| **Eligible!** |
| --- |

That is great news! If you are willing to take part in the study, we will need to click through to the next page and read our participant information sheet and provide consent. This will help you make a decision about whether you do want to participate or not, so please read all information carefully.

Please remember you do not have to participate if you don’t want to, and you can withdraw your consent at any time.

If you’ve had a tough time with your mental health lately, we encourage you to talk to a local doctor or mental health professional about how you’re feeling.

If you would like to know where to get some immediate help, here are some suggestions:

Lifeline: [name]

Kids Helpline: [name]

Suicide Callback Service: [name]

For 24 hour advice on what to do and who to contact, don’t hesitate to visit HealthDirect

( <https://www.healthdirect.gov.au/>) or call them on [name].

They can help you figure out the best people to contact in your local area

**If you feel in danger or that you might hurt yourself, do not hesitate to call Emergency Services on 000.**

(**If ineligible)**

Ok great, thank you for your interest in our study.

Based on your responses, it looks like you are:

| **Ineligible** |
| --- |

Thank you for your interest in our study.

Based on your responses, your participation in this study is now complete.

[response 1] Your responses indicate that you are unable to participate in this study because you don’t meet the selection criteria.

[response 2] Your responses indicate that now is not the best time for you to participate in this study because participating at this time might cause you to become distressed, or uncomfortable.

Your willingness to participate in this study is hugely appreciated. And just because this might not be the right study for you, or the right time for you to participate, it does not mean you are on your own.

If you’ve had a tough time with your mental health lately, we encourage you to talk to a local doctor or mental health professional about how you’re feeling.

If you would like to know where to get some immediate help, here are some suggestions:

**Lifeline:** [name]

**Kids Helpline:** [name]

**Suicide Callback Service:** [name]

For 24 hour advice on what to do and who to contact, don’t hesitate to visit HealthDirect

( https://www.healthdirect.gov.au/ ) or call them on [name].

They can help you figure out the best people to contact in your local area.

If you feel in danger or that you might hurt yourself, do not hesitate to call Emergency Services on 000.

# Appendix C: Survey Measures

| **What the participant will see** | | **Drop down response options available** |
| --- | --- | --- |
| Age | --- select ---- | 16  17  18  19  20  21  22  23  24  25 |
| Gender identity | --- select ---- | Female  Male  Non-binary  Different identity |
| Gender assigned at birth | --- select ---- | Female  Male |
| Where do you live? | -- select ---- | NSW  QLD  VIC  TAS  SA  WA  NT  ACT |
| Rural/remote or metropolitan | -- select ---- | Rural and/or remote  Metropolitan |
| Do you identify as being Lesbian, Gay, Bisexual, Transgender, or Intersex? | -- select ---- | No  Lesbian  Gay  Bisexual  Transgender  Intersex  Prefer not to say |
| Indigenous status | -- select ---- | Not Aboriginal or Torres Strait Islander  Yes - Torres Strait Islander Yes – Aboriginal  I prefer not to say |
| Language/s spoken at home | -- select ---- | English only  English and other language  Another language only |
| Current living situation | -- select ---- | Live alone  Live with parent/s/family,  Live with a significant other  Live with roommate(s)  Other |
| Current relationship situation | -- select ---- | Not in a relationship  Boyfriend/Girlfriend  De facto/married Separated  Divorced or Widowed  Other |
| Highest level of education | -- select ---- | Primary school  Years 7 to 9  Year 10 or equivalent  Year 11  Year 12 or equivalent  Certificate Level I - IV Diploma/Associate Degree  Graduate Diploma/Certificate  Bachelor Degree  Master degree  Doctoral degree |
| What is your current employment status? | -- select ---- | Full-time  Part-time  Casual  Self-employed  Unemployed |
| Has your current employment status changed as a result of the coronavirus (COVID-19) pandemic? | --- select ---- | Yes  No |
| Have you ever experienced mental illness or been diagnosed with mental illness? | -- select ---- | Yes  No  I don’t know. |
| Have you ever seen a mental health professional (psychologist, psychiatrist) for a mental health problem? | --- select ---- | Yes  No  I don’t know. |
| Have you previously used any health or wellbeing apps on your smartphone? | --- select ---- | Yes  No  I don’t know. |

**Suicidal Ideation Attributes Scale (SIDAS)**

**Now we’re going to ask you some questions are about your suicidal thoughts, and the severity of them.**

**Please think about the past month when answering the following questions.**

##

| In the past month, how often have you had thoughts about suicide? | | | | | | | | | | |
| --- | --- | --- | --- | --- | --- | --- | --- | --- | --- | --- |
| 0  Never | 1 | 2 | 3 | 4 | 5 | 6 | 7 | 8 | 9 | 10  Always |
| In the past month, how much control have you had over these thoughts? | | | | | | | | | | |
| 0  No control | 1 | 2 | 3 | 4 | 5 | 6 | 7 | 8 | 9 | 10  Full control |
| In the past month, how close have you come to making a suicide attempt? | | | | | | | | | | |
| 0  Not close | 1 | 2 | 3 | 4 | 5 | 6 | 7 | 8 | 9 | 10  Made an attempt |
| In the past month, to what extent have you felt tormented by thoughts about suicide? | | | | | | | | | | |
| 0  Not at all | 1 | 2 | 3 | 4 | 5 | 6 | 7 | 8 | 9 | 10  Extremely |
| In the past month, how much have thoughts about suicide interfered with your ability to carry out daily activities, such as work, household tasks or social activities? | | | | | | | | | | |
| 0  Not at all | 1 | 2 | 3 | 4 | 5 | 6 | 7 | 8 | 9 | 10  Extremely |

**We’d just like to ask you a few more questions about prior self-harm behaviour. Just to remind you, these questions are completely voluntary.**

| **What the user will see** | | **Drop down response options available** |
| --- | --- | --- |
| Have you ever attempted suicide? | --- select ---- | No, never Yes, once  Yes, more than once |
| If more than once, how many times? | --- select ---- | 2  3  4  5  6+ |
| How many months have you been thinking about suicide? | --- select ---- | 1 or less  2  3 to 6  >6 to 12  >12 to 24  >24 to 36  >36 |
| How often, on average, do you think about suicide? | --- select ---- | Daily Weekly Monthly  Less than monthly |
| Have you attempted suicide in the past 30 days? | --- select ---- | No, never Yes, once  Yes, more than once |
| Have you ever injured yourself on purpose (i.e., intentional, self-inflicted damage to the surface of the body without suicidal intent) | --- select ---- | No, never  Yes, once  Yes, more than once |
| In the past month, how often have you injured yourself on purpose? | - If ‘Yes, more than once’ then select - | 2-5 times (low)  6-9 times (moderate)  10-20 times (high)  20+ times (severe) |
| Please rate how serious your worst injury was in the past month | - If ‘Yes, once’ or ‘yes, more than once’ then select - | No care was needed (mild)  Some care was needed (moderate)  I required medical care (severe) |

| If you are feeling distressed, please contact any of the following numbers |
| --- |
| Lifeline  [name] |
| Kids Helpline  [name] |
| Suicide Callback Service  [name] |

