# Study Design

## 3.1. Treatment Design

The flowchart (Figure 1) summarizes this study which will consist of evaluating the efficacy of a digital therapeutic for suicidal ideation, using a is a two-arm, parallel, double-blind superiority randomised controlled trial design. Following completion of the baseline (T0) assessment, participants will be randomised at equal allocation (2:2) to one of two smartphone applications, a DBT-based application (LifeBuoy) or a placebo (non-therapeutic) control application (LifeBuoy-C). After completion of the 6 week intervention, primary, secondary and tertiary outcomes will be assessed at immediate post-intervention (T1) and then at 4-months post-intervention (T2). All surveys will be completed online, with survey links distributed automatically to registered participants using Black Dog Institute’s research engine. Subjects in the intervention condition will be invited to participate in a qualitative intervention at the final assessment to understand their experience with the LifeBuoy application.

[figure not shown]

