## 6.2. Secondary outcome measures

**Suicide Behaviours**

Participants’ previous suicide attempts and self-injury are assessed by eight questions developed for a previous suicide prevention trial [23]. Participants are invited to indicate whether they have attempted suicide in their lifetime and in the past 30 days on a three-point Likert scale, ranging from ‘No, never (0)’, ‘Yes, once (1)’, to ‘Yes, more than once (2)’. They are also asked to report the number of suicide attempts over their lifetime, and the number of months that they have been thinking about suicide. Apart from that, participants are asked to indicate whether they have intentional self-injury in their lifetime on the aforementioned three-point Likert scale. If yes, they are asked to provide the number of times of their intentional self-injury and rate the severity of the worst injury in the past month on a three-point Likert scale, ranging from ‘No care was needed (1)’, ‘Some care was needed (2)’, to ‘Required medical care (3)’.

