# Sample size

Based on a systematic review and meta-analysis [8], an effect size of 0.30 (Cohen’s d) will be expected between the intervention condition and the control condition at post-test in terms of suicidal ideation as measured by the SIDAS (Appendix C). Based on an attrition rate of 30% and a 0.50 correlation between pre- and post-test SIDAS scores, a sample size of n = 189 in each condition (total N = 378) will detect this expected effect size with power = 0.80 and alpha = 0.05. The planned sample size of n = 189 for the intervention condition will also allow statistical power of at least 0.80 to detect small-to-medium size effects in moderation analyses.

For the qualitative interviews we aim to recruit 10% of participants from the Intervention condition. This will result in a subsample of qualitative interviews of approximately n=20 persons based on a recruitment target of n=189 in each condition. In prior qualitative studies that have examined users’ experience with an app for managing psychological and physical health conditions, the sample sizes ranged from between 15 and 25 participants [41 – 43] which indicates our sample size is acceptable and justifiable.

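### For people with any lifetime self-injury, the Appendix C items cannot validly record zero past-month episodes, and the frequency item cannot record one

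*Protocol*

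**What the plan says.** Section 6.2 lists Suicide Behaviours, covering attempts and self-injury, among the secondary outcome measures. On self-injury it describes a lifetime question and then states: "If yes, they are asked to provide the number of times of their intentional self-injury", followed by a rating of the worst injury in the past month. Section 3.1 says that secondary outcomes are assessed at post-intervention (T1) and again at the final follow-up (T2).

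Appendix C prints the items directly after the SIDAS. They are introduced as "a few more questions about prior self-harm behaviour", and participants are told that "these questions are completely voluntary". Three items concern self-injury:

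- A lifetime item, answered never, once or more than once.
- A frequency item, "In the past month, how often have you injured yourself on purpose", shown only after the lifetime answer more than once. Its options are 2-5, 6-9, 10-20 and 20+ times.
- A severity item, "Please rate how serious your worst injury was in the past month", shown after either lifetime yes. Its options are mild, moderate and severe.

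**The concern.** A lifetime question gates a past-month count. Options that start at two suit a gate of more than once only when both cover the same period. The lifetime attempt items in the same block do this correctly: more than once leads to a lifetime count that starts at 2. For self-injury the periods differ, so someone who self-injured repeatedly years ago and not at all last month is shown a list with no truthful answer. The routing also differs from Section 6.2, which asks for the number of times after any yes.

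The stake is change after baseline. A participant who stops self-injuring has no answer that says so, and one who falls from several episodes to one cannot enter that count. Any past-month figure would then depend on how blanks and forced answers were handled. An analysis plan cannot recover what the survey did not collect.

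**Working it through.** The plan states no figure on this point, so there is none to reproduce. The check is to set every possible state of a respondent against the printed routing and options.

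**Step 1: the frequency and severity items, state by state** (Appendix C)

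| Lifetime answer | True past-month count | Frequency options that fit | Severity item |
|---|---|---|---|
| never | 0 | not shown; zero is implied | not shown |
| once | 0 | not shown | shown, no valid answer |
| once | 1 | not shown | shown, valid |
| more than once | 0 | none | shown, no valid answer |
| more than once | 1 | none | shown, valid |
| more than once | 2-5 | one | shown, valid |
| more than once | 6-9 | one | shown, valid |
| more than once | 10-19 | one | shown, valid |
| more than once | 20 | two (10-20 and 20+) | shown, valid |
| more than once | over 20 | one | shown, valid |

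Leaving out never, there are 9 states. The frequency item has exactly one matching option for 4, none for 4 and two for 1 (4 + 4 + 1 = 9). None of the three items can record zero past-month episodes for someone with prior self-injury. This counts states and says nothing about how many participants fall in each.

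**Step 2: what the items carry together.** An answered severity item after lifetime once fits one past-month episode. After more than once, a blank frequency with an answered severity also fits one episode, and two blanks fit zero. These readings need every respondent to skip consistently. Since the items are voluntary, two blanks equally fit a refusal. A move in the lifetime answer between surveys (never to once, or once to more than once) shows a new episode since the last survey. From day 0 to day 42 (Section 6.5) that window is longer than a month, and nobody already at more than once can move.

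**Step 3: what the collected data could bound.** Let N be the respondents in an arm, L those with lifetime self-injury and F those choosing 6-9 or more. Assume that nobody with 0 or 1 past-month episodes picks above the lowest option. Using the lifetime and frequency items, past-month prevalence then lies between F/N and L/N.

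**Step 4: illustration.** The documents give no self-injury rates, so every rate here is assumed. Let a be the share answering more than once, and q the share of those with 0 or 1 past-month episodes. The true share with two or more episodes is a × (1 − q). If everyone shown the item picks a printed option, the recorded share is a, whatever q is.

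| a | q = 30% | q = 50% | q = 70% | Recorded |
|---|---|---|---|---|
| 30% | 21% | 15% | 9% | 30% |
| 50% | 35% | 25% | 15% | 50% |
| 70% | 49% | 35% | 21% | 70% |

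The error can also go the other way. Section 8 implies about 189 × 0.70 = 132 respondents per arm at post-test. Suppose 66 have lifetime self-injury: 16 once (14 with 0 and 2 with 1 in the past month) and 50 more than once (30 with 0, 8 with 1, 12 with 2 or more). True past-month prevalence is (2 + 8 + 12)/132 = 16.7%. On the frequency item alone, counting blanks as none gives 12/132 = 9.1%, and forced lowest answers give 50/132 = 37.9%. The finding rests on Step 1, not on these counts.

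**The case against.** The strongest reply is that no past-month self-injury rate or arm comparison is planned. Section 6.2 describes the items as covering previous behaviour and gives no period for the number of times. Self-injury is absent from the secondary aim (Section 1.2), the hypotheses (Section 1.4) and the outcomes named in Section 7, and the schedule in Section 6.5 has no row for it. All of this stands and limits the impact. It does not remove the defect. The measure is still listed as a secondary outcome, Section 3.1 has secondary outcomes assessed at T1 and T2, and both follow-on items explicitly ask about the past month. The charter's Safety Analyses section (Appendix E) takes recent attempts from a post-intervention or follow-up survey question in this same block, which supports repeat use.

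It is also fair that the items are not empty. Never implies zero, and the severity item carries some information about single episodes, as Step 2 shows. The claim is therefore confined to people with prior self-injury. Section 6.2 says the questions were developed for an earlier suicide prevention trial. Whether the routing follows that source cannot be checked here, and it would not supply the missing answers.

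A reader might also infer a gap in safety monitoring, because the charter gives self-harm above expected rates as a reason to request unblinded data, while its lists name only SIDAS and attempts as outcomes. The documents do not support that. The phrase is only an example, and self-harm can include attempts, since Appendix C uses the term for both. Self-injury could also reach the board through adverse event data, risk alerts, follow-up data by group or a request. The report shell that the charter mentions is not at hand.

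**Conclusion.** The concern holds for participants with any lifetime self-injury. Zero past-month episodes cannot be validly recorded on any item, one episode cannot be recorded on the frequency item, and exactly 20 fits two options. Past-month self-injury, one component of a listed secondary measure, is not cleanly measurable at T1 or T2. This follows from the printed routing and options and needs no assumed rate. How far a reported rate would be off, and in which direction, cannot be known from the documents.

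The consequence is limited. The SIDAS primary outcome and the analyses named in Section 7 are untouched. The 30-day attempt item is sound, since it offers never, once and more than once. It would go too far to say that the survey cannot record zero for anyone, or that a planned treatment comparison fails.

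**What to change.** In Appendix C, show the past-month frequency item to everyone with any lifetime self-injury, with options none, once, 2-5, 6-9, 10-19 and 20+. Ask the severity item only after one or more past-month episodes. Each of the nine states in Step 1 then has exactly one answer, and the routing agrees with Section 6.2.

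The cost is a small edit to two items and their branching, plus an ethics amendment. Answers already collected under the old item cannot be pooled with new ones, so a change during the trial splits the series.

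Optionally, the charter could say whether self-harm includes self-injury, and name self-injury by arm in the closed report. That is a clarification, not the correction of an error, and it would mean revising a charter that the board's members approve.
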